## Aim

To determine the effect of lifestyle intervention during pregnancy on obesity, markers of metabolic syndrome and bone mineralization of 2.5-3 year old children of obese mothers.

To assess the effect after controlling for maternal and perinatal factors.

## Background

Over weight and obesity are increasing problems worldwide. These conditions lead to an increased risk of a series of severe diseases – such as cardio-vascular disease, diabetes and cancer (1). In many cases obesity is also associated to risk factors such as insulin resistance, hypertension and dyslipidemia – the so called metabolic syndrome. (2). The mechanism behind this is traditionally considered interplay between genetic and environmental factors, but newer studies has suggested, that epigenetic modulation as a result of the intrauterine and postnatal milieu has an independent role (fetal/neonatal programming).

In Denmark 1/3 of all pregnant women are overweight (body mass index (BMI) >= 25 kg/m2), and 12 % are obese (BMI >= 30 kg/m2) (3), and their children have an increased risk of being born large for gestational age and of developing obesity in childhood, adolescence and adulthood.

Birth weight is often used as a surrogacy for fetal growth and nourishment. About 20 years ago, the English researches Barker and Hales reported that low birth weight predisposed to glucose intolerance, insulin resistance, hypertension and cardiovascular disease decades later in life (4, 5). On this background, they put forth the birth weight hypothesis (”the thrifty phenotype hypothesis”) in which malnourishment in fetal life leads to a programming of energy conserving mechanisms (6). These mechanisms are inappropriate if the individual is exposed to ordinary western lifestyle and increases the risk of for instance Type 2 diabetes. Low birth weight in combination with rapid postnatal growth is especially a problem (7). Many epidemiological human studies as well as animal studies have shown that also high birth weight is associated with Type 2 diabetes and long term risk of obesity, with insulin resistance playing an essential role (8, 9, 10). Furthermore, high birth weight is associated with increased risk of several forms of cancer (11), and type Type 1 diabetes (12).

High birth weight is especially seen if the mother has diabetes, pregestational obesity and/or excessive gestational weight gain. Maternal obesity is an independent risk factor for a series of diseases/adverse outcomes in their offspring: obesity, dyslipidemia, glucose intolerance, high HbA1c and hypertension (10, 13, 14). Excessive gestational weight gain is also associated with increased BMI, blood pressure and adiposity (15).

Adiposity in children can be determined using measures of BMI, skinfolds and abdominal circumference, but also by using DEXA scans.

Pregestational obesity is also associated with low 25-OH-vitD in both mother and child (16). This can have long term consequences as low vitamin D status influences a range of mechanisms including development of organs and the immune system. Studies have thus shown, that supplements of vitamin D given to pregnant women and infants reduces the risk of asthma in childhood (17,18,20) and of Type 1 diabetes in adulthood (19), whereas smaller studies have suggested a negative effect of vitamin D on asthma and atopic dermatitis at the age of 9 (21). Maternal 25-OH-vitD is highly correlated to 25-OH-vitD in the umbilical cord (22, 23,24, 25). And umbilical cord 25-OH-vit D is thus considered a good proxy for fetal 25-OH-vit D status.

Maternal over weight/obesity and gestational weight gain are potentially modifiable risk factors, which in theory can be prevented by securing optimal gestational weight gain. Therefore, it is key to focus on possible interventions, which can limit gestational weight gain.

The present study´s first part (study A) is a follow-up on an ongoing lifestyle intervention study at Odense University Hospital and Aarhus University Hospital, Denmark, the Lifestyle in pregnancy (LiP) study. The project is registered at www.clinicaltrials.gov (26). In the LiP project 360 obese pregnant women (pregestationel BMI >= 30 kg/m2) were randomized to lifestyle intervention with diet and exercise guidance or routine control. The aim was to limit the gestational weight gain and thereby limiting pregnancy- and birth complications. The inclusion criteria were: singleton pregnancies (nulli- and multipara) with pregestational BMI >=30 kg/m2, age 18-40 years and normal oral glucose tolerance test (OGTT).

Exclusioncriteria were: multiple pregnancies, chronic disease (for instance asthma, rheumatoid disease, inflammatory bowel disease, diabetes, alcohol- or substance abuse and non-Caucasians).

Results from the RCT are not yet available. Therefore, it is not known whether the RCT will result in significant effects on either maternal or fetal outcomes. Regardless of the results, it is interesting to determine the effect of the intervention on the growth, metabolism and diseases in the offspring in a follow-up study (study A).

In another part of the study, Study B, we wish to compare children of the non-intervention group of pregestational obese mothers to a reference-group of children born to normal weight mothers, born in the same time period. In this part, we will study the effects of pregestational obesity.

**Hypothesis**

**Study A (follow-up of RCT):**

Intervention with diet and exerzice has possitive effects on offspring health at the age of 2.5-3 years in terms of:

1. Obesity(via fetal programming – excess nutrients).
2. Markers of later metabolic syndrome (via fetal programming – excess nutrients).
3. Bone mineralization (via effect of fetal vitamin D status)

**Study B:**

Pregestational obesity effects the offspring at the age of 2.5-3 years in terms of:

1. Obesity(via fetal programming – excess nutrients).
2. Markers of later metabolic syndrome (via fetal programming – excess nutrients).
3. Bone mineralization (via effect of fetal vitamin D status)

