**Study B:**

Design:

Observational study of 2 groups with the exposition variable +/- pregestationel maternel obesity.

Inclusion criteria:

Children born to mothers who were part of the control group in the LiP study, called the exposed group. Singleton children born to mothers who were normal weight pregestationally (BMI 18,5-24,9 kg/m2), age 18-40 years, normal OGTT and no exclusion criteria from the LiP study, called the reference group.

Exclusion criteria:

Congenital anomalies and chromosome defects.

Numbers:

With an estimated drop-out form the LiP study of 50 % a maximum of 90 children can be included in the exposition group. The reference group must also be 90 children.

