***Measures, studies A og B:***

1. 25-OH-Vit D analyses on umbilical cord blood (study A).
2. Questionnaires at 12, 24 and 30-36 months of age. Data: early feeding patterns, breastfeeding patterns etc., exposition to smoking, parental height and weight. The earliest included children will however, not be included in the 12 months questionnaire.
3. Data of early growth- collected from general practitionars.
4. Clinical exam at the age of 30-36 months. Height, weight, abdominal circumference, subscapular and triceps skinfolds and blood pressure.
5. Venous blood sample at the age of 30-36 months: fasting blood glucose, insulin, C-peptide, HbA1c and lipids.
6. DEXA scan for fat mass and mineralization.

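### Study B attributes differences in child obesity and metabolic markers to fetal programming, but its observational contrast cannot separate that route from inheritance and home, and the parental size data it collects have no named use.

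*Protocol*

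**What the plan says.** The Study B hypothesis in the protocol reads "Pregestational obesity effects the offspring at the age of 2.5-3 years in terms of" three outcome domains. The first is "Obesity(via fetal programming – excess nutrients", and the same route is given for markers of later metabolic syndrome. Bone mineralization is credited to fetal vitamin D status instead. The Background describes the purpose in similar terms: "In this part, we will study the effects of pregestational obesity".

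Under Materials and methods, Study B is an "Observational study of 2 groups with the exposition variable +/- pregestationel maternel obesity". The exposed children come from the control arm of the LiP trial, which enrolled "singleton pregnancies (nulli- and multipara) with pregestational BMI >=30 kg/m2". The reference group is "Singleton children born to mothers who were normal weight pregestationally (BMI 18,5-24,9 kg/m2". The target is 90 children per group.

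The Background itself names the rival explanation for obesity and its metabolic risk factors: "The mechanism behind this is traditionally considered interplay between genetic and environmental factors". It presents programming as a newer, independent contribution.

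On adjustment, the Aim mentions controlling for factors on the mother's side and around birth. The Statistics section describes its 0.42 SDS target as already corrected for confounders. Statistical analyses promises regression for confounders without naming any. The questionnaires collect "exposition to smoking, parental height and weight", among other items, and no section says how parental size will be used.

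**The concern.** Study A can use causal wording because the mothers were randomised. Study B uses the same wording, with the same bracketed routes, for a contrast that was not randomised. A child of an obese mother inherits her genes and grows up in her household as well as having developed in her uterus. A two-group difference in BMI SDS is the sum of these and does not show which route produced it.

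The adjustment that is described does not obviously help. Paternal BMI is neither a maternal nor a perinatal factor, so the Aim's wording leaves it out. The one analysis assigned specifically to Study B is by gestational weight gain, which does not address inheritance or home.

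What is at stake is the interpretation. A clear difference between the groups could be reported as support for the stated mechanism when part or all of it has another source. The group comparison remains valid as an association.

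**Working it through.** **Reproducing the plan's figure.** Inputs from Statistics: n = 90 per group, 1.96, 0.84, SD 1. The detectable difference is √(2/90) × (1.96 + 0.84) × 1 = 0.1491 × 2.80 = 0.417. This agrees with the protocol and is not in dispute.

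**Gap in maternal BMI between the groups.** The Background gives one third of pregnant women at BMI 25 or above and 12% at 30 or above. The matching standard normal quantiles are 0.4307 and 1.1750. I fitted two distributions to these points and took the mean above 30 and the mean between 18.5 and 24.9.

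- Normal: SD = 5/(1.1750 − 0.4307) = 6.718, mean 22.106. Group means are 33.305 and 21.730, so the gap is 11.575/6.718 = 1.72 SD.
- Log-normal, gap in kg/m²: log-scale SD = ln(30/25)/(1.1750 − 0.4307) = 0.245, median 22.50, SD 5.765 kg/m². Group means are 34.035 and 21.656, so the gap is 12.379/5.765 = 2.147 SD.
- Log-normal, gap on the log scale: 1.84 SD, between the other two.

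The range is therefore about 1.7 to 2.1 SD.

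**Difference expected with no intrauterine effect.** Let r be the rise in child BMI SDS per SD of maternal BMI through genes and home only. The documents give no value, so r is an assumption run over a range. Expected difference = r × gap. The chance of p<0.05, unadjusted, is Φ(d/0.1491 − 1.96) + Φ(−d/0.1491 − 1.96).

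| r (assumed) | Difference at gap 1.72 | P(p<0.05) | Difference at gap 2.147 | P(p<0.05) |
|---|---|---|---|---|
| 0.10 | 0.17 | 21% | 0.21 | 30% |
| 0.15 | 0.26 | 41% | 0.32 | 58% |
| 0.20 | 0.34 | 64% | 0.43 | 82% |
| 0.25 | 0.43 | 82% | 0.54 | 95% |

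The full 0.417 is reached at r = 0.417/1.723 = 0.24, or r = 0.417/2.147 = 0.19.

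**What a maternal-versus-paternal comparison could show.** Assume residual SD 1, 180 families with complete data, and both parental BMIs with SD 1 in the sample and correlation ρ. In a mutually adjusted model the standard error of the slope difference is √(2/(180 × (1 − ρ))).

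- ρ = 0: SE 0.105; detectable with 80% power, 2.8 × 0.105 = 0.30 per SD.
- ρ = 0.2: SE 0.118; detectable 0.33 per SD.
- If maternal BMI has SD 1.2 because the groups are sampled from separate ranges, with ρ = 0: SE = √((1/1.44 + 1)/180) = 0.097; detectable 0.27 per SD.

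These detectable differences exceed the whole assumed range of r (0.15 to 0.25), and missing paternal data would raise them.

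**The case against.** The strongest reply is that confounder control is already planned. The 0.42 SDS target is defined as corrected for confounders, regression is promised, and parental height and weight are collected. The covariate list may sit in a statistical analysis plan that is not shown. This stands in part. A reader might infer that paternal BMI has been given no role, but the documents support only that it has no *named* role. The probabilities above are for an unadjusted comparison, whereas the target is an adjusted one. What remains is the hypothesis wording, which the protocol itself fixes. Adjustment for measured variables, paternal BMI included, would still not remove maternal genes or the whole home environment.

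Four stronger readings are tempting and should not be made:

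- **That Study B would be declared positive for fetal programming.** No section contains such a decision rule. The routes are bracketed rationale attached to hypotheses, and the design is openly labelled observational.
- **That genes and home alone would produce the target difference.** This depends on an assumed r of about 0.19 to 0.24 or more, and on an analysis that does not remove it. A reader might also guess a gap of up to 3 SD between the groups, but the Background figures do not support that.
- **That the excess-nutrient criticism covers all three hypotheses.** Bone is credited to vitamin D, so it applies to the first two only.
- **That parental education is not collected.** The questionnaire list is expressly open-ended, so this cannot be inferred.

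It is also fair to object that a paternal comparison is weak. It would often be inconclusive, and a larger maternal association could arise after birth, for example through feeding. It therefore cannot license a claim of an intrauterine effect.

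**Conclusion.** The point holds as one of interpretation and analysis. Study B attaches a specific mechanism to two hypotheses that its design cannot isolate, and it leaves relevant data without a stated use.

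The size is conditional. With r assumed at 0.15 to 0.25 and a gap of 1.7 to 2.1 SD, genes and home alone would give an unadjusted difference of 0.26 to 0.54 SDS and a 41% to 95% chance of p<0.05. At r = 0.10 the chance is still 21% to 30%, against a nominal 5%. These figures rest on four assumptions:

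- the fitted BMI distributions describe both groups;
- the slope is linear;
- child BMI SDS has SD 1;
- there is no adjustment.

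Confounder adjustment would lower them by an amount the documents do not allow one to state. The sample size calculation is correct.

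**What to change.** 1. Reword Study B's hypotheses 1 and 2, and the conclusions to be drawn from them, as associations with maternal pregestational obesity. Fetal programming can stay in the Background as one possible explanation.
2. Confirm that the parental height and weight items cover the father.
3. Name paternal BMI as a covariate in the adjusted Study B model.
4. Pre-specify one mutually adjusted model with maternal and paternal BMI, and report the difference between their associations with its confidence interval. Label it supportive evidence only, with no rule under which an intrauterine contribution would be claimed.

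This needs changes of wording and analysis, and no extra children, visits or blood samples. The drawbacks are that some paternal data will be missing or only reported, and that precision is low: 80% power only for a slope difference of about 0.3 per SD with complete data.

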**Materials and methods:**

**Study A:**

Design:

Randomized controlled trial. Prospective follow-up.

Inclusion criteria:

Children born to mothers, who participated in the LiP study in Odense University Hospital or Aarhus University Hospital.

Numbers:

Estimated drop-out of the LiP study is 50%. This study will thus contain:

- Children born to obese mothers who participated in lifestyle intervention during pregnancy (n=90)
- Children born to obese mothers who did not participate in lifestyle intervention (n=90)

**Study B:**

Design:

Observational study of 2 groups with the exposition variable +/- pregestationel maternel obesity.

Inclusion criteria:

Children born to mothers who were part of the control group in the LiP study, called the exposed group. Singleton children born to mothers who were normal weight pregestationally (BMI 18,5-24,9 kg/m2), age 18-40 years, normal OGTT and no exclusion criteria from the LiP study, called the reference group.

Exclusion criteria:

Congenital anomalies and chromosome defects.

Numbers:

With an estimated drop-out form the LiP study of 50 % a maximum of 90 children can be included in the exposition group. The reference group must also be 90 children.

***Measures, studies A og B:***

1. 25-OH-Vit D analyses on umbilical cord blood (study A).
2. Questionnaires at 12, 24 and 30-36 months of age. Data: early feeding patterns, breastfeeding patterns etc., exposition to smoking, parental height and weight. The earliest included children will however, not be included in the 12 months questionnaire.
3. Data of early growth- collected from general practitionars.
4. Clinical exam at the age of 30-36 months. Height, weight, abdominal circumference, subscapular and triceps skinfolds and blood pressure.
5. Venous blood sample at the age of 30-36 months: fasting blood glucose, insulin, C-peptide, HbA1c and lipids.
6. DEXA scan for fat mass and mineralization.

**Outcomes:**

1. Studies A og B´s primary outcomes are child BMI SDS (z-score)
2. Secondary outcomes:

a) Abdominal circumference, abdominal circumference:height ratio, subscapular- and triceps-skinfolds, fat percentage by DEXA scan. Bonemineralization by DEXA scan.

b) F-blood glucose, insulin, C-peptide, insulin: glucose ratio, C-peptide: glucose ratio, HOMA index, lipids, 25-OH-vit D and blood pressure for assessment of markers of metabolic syndrome.

**Statistics:**

Power calculation is based on an estimated dropout of 50 % from the LiP study, n = 90 in each group.

BMI SDS:

N in each group is 90, Z2α=1.96 (significance level. p=0.05) and Z2β=0.84 (strength β=0.80), SD=1, true difference in outcome δ1 is X.

This is used in the formula:

n > 2 (((Z2α + Z2β )*SD)/ δ1))2 (27).

And:

n > 2 (((1.96+0.84)*1)/X))2,

which means X= 0.417.

This means, that the study has enough power, if the true difference between (a) intervention group and og non-intervention group of obese pregnant women and between (b) non-intervention group and reference group, is 0,42 SDS – corrected for confounders.

There are no previous studies to base this power calculation on.

**Statistical analyses**

Outcomes will be analyzed according to pregestational BMI *(Study A)* and gestational weight gain *(Study B).* Data will also be analyzed with regression models for controlling of confounders.

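### The grouping variables in the analysis section do not match the comparisons that the protocol designs and powers, and swapping the study labels would still leave Study A without its randomised comparison

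*Protocol*

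**What the plan says.** The protocol's section headed Statistical analyses has two sentences. The first gives the variable by which each study is analysed: "Outcomes will be analyzed according to pregestational BMI *(Study A)* and gestational weight gain *(Study B"). The second adds: "Data will also be analyzed with regression models for controlling of confounders". It names no arm, exposure or group.

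The rest of the protocol describes different comparisons.

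- **Study A.** The design is given as "Randomized controlled trial. Prospective follow-up", and the hypothesis is "Intervention with diet and exerzice has possitive effects on offspring health at the age of 2.5-3 years". The power calculation under Statistics applies "if the true difference between (a) intervention group and og non-intervention group of obese pregnant women" reaches the detectable size.
- **Study B.** The design is "Observational study of 2 groups with the exposition variable +/- pregestationel maternel obesity". The second powered difference is between "b) non-intervention group and reference group, is 0,42 SDS".

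The Background section adds two relevant facts. All mothers in the LiP trial had a pregestational BMI of at least 30 kg/m2, and the trial's purpose was to limit gestational weight gain. The primary outcome in both studies is child BMI SDS.

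**The concern.** The variable named for each study is not the one that defines its comparison.

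In Study A, pregestational BMI is a baseline characteristic, and every mother is at or above 30. It does not separate the randomised arms. An analysis by BMI describes how child BMI SDS varies with the degree of maternal obesity, which is an observational question. It does not estimate what the intervention did.

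In Study B, the declared exposure is pregestational obesity. Gestational weight gain arises after that exposure, may be influenced by it, and does not define the two groups.

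What is at stake is the primary analysis of both studies. Three groupings for Study A can be drawn from the protocol: by arm (from the design), by pregestational BMI (from the paragraph as written), and by gestational weight gain (from the paragraph with its labels exchanged). Only the first keeps the protection of randomisation. Leaving all three open lets the choice be made after the data are seen.

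**Working it through.** **1. The protocol's own figure.** The inputs come from the Statistics section: 90 children per group, z = 1.96 (two-sided 5%), z = 0.84 (80% power), SD = 1. The 90 follows from the 360 women randomised (Background) and the assumed 50% dropout: 360 × 0.5 / 2 = 90.

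Solving the stated formula n = 2 × ((1.96 + 0.84) × SD / X)² for X:

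X = (1.96 + 0.84) × 1 × √(2/90) = 2.8 × 0.1491 = 0.417

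This reproduces the stated 0.417, rounded in the text to 0.42. In the other direction, 90 per group gives power 0.799 at a difference of 0.417 and 0.804 at 0.42. The required sample size is 91 per group at 0.417 and 89 at 0.42. The arithmetic is sound.

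**2. What the figure applies to.** The factor 2/n is the variance of a difference between two means with n children in each group. The 0.42 SDS therefore belongs to a comparison of two groups of 90. An analysis by BMI within Study A, or by weight gain within Study B, has a different effect measure (a slope, or a difference between categories that the protocol does not define). Its precision depends on the spread of that variable, which the protocol does not give.

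**3. The sections side by side.**

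| | Study A | Study B |
|---|---|---|
| Hypothesis | effect of the intervention | effect of pregestational obesity |
| Design | follow-up of a randomised trial | two groups, obese v normal weight before pregnancy |
| Powered contrast | intervention v non-intervention | non-intervention v reference |
| Analysis section, as written | pregestational BMI | gestational weight gain |
| Analysis section, labels exchanged | gestational weight gain | pregestational BMI |

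**4. As written.** Neither variable is the one that forms the comparison in the rows above it.

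**5. With the labels exchanged.** Study B is largely repaired. Its groups are defined by pregestational BMI (at least 30 against 18.5 to 24.9 kg/m2), so an analysis by BMI separates them, although the two-group form would still need to be stated. Study A is not repaired. Weight gain is observed after randomisation and is what the intervention set out to change. Women with equal weight gain in the two arms are no longer a randomised comparison, and part of any effect on the child may pass through weight gain.

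**6. The regression sentence.** It provides for confounder control without naming the effect to be estimated, so it does not settle the matter. The Aim section plans control for maternal and perinatal factors without listing them, so adjustment for weight gain is not excluded.

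**The case against.** The strongest reply is that nobody reading the whole protocol could mistake the intention. The aim, hypotheses, designs and power statement all point to the same two contrasts, and the power statement refers to differences corrected for confounders. On that view the regression sentence takes its exposure from those sections, and the first sentence only lists supplementary breakdowns, possibly with the labels reversed.

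Much of this stands. The intended comparisons are recoverable, and transposed labels are a plausible explanation. Two things remain. The analysis section does not call its groupings supplementary; it gives them first and adds the regression as a further step. And exchanging the labels does not put the randomised arm into Study A.

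A second reply is that modelling detail belongs in a statistical analysis plan, which may exist. That is right for covariates and model form, and none is called missing here. It does not cover a stated analysis that conflicts with the design: a plan that followed this paragraph would carry the error forward, and one that departed from it would contradict the protocol.

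Stronger readings should be resisted:

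- A reader might infer that the protocol plans neither comparison at all, or count both powered contrasts as lost. The documents do not support this. Both are stated repeatedly outside this paragraph, and Study B is largely restored if the labels were swapped.
- A reader might infer from the list of measures that weight gain is unavailable for the reference mothers. That list is mainly of child measures and its questionnaire item is open-ended, so its silence shows nothing.

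**Conclusion.** The paragraph is wrong as written and must be corrected. Its grouping variables conflict with the hypotheses, designs and powered contrasts of the same protocol, and its regression sentence does not resolve the conflict.

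The conclusion is firmest for Study A: on either reading of the labels, the analysis named is not the comparison of randomised arms. For Study B it depends on taking the labels as printed.

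The consequence is one of kind. Followed literally, Study A yields no intervention effect, and the 0.42 SDS statement describes a test that the analysis section does not name. No bias or loss of power can be quantified from the documents, and the sample size calculation itself is not in error. The conclusion rests on the current text and on the stated purpose of the LiP intervention, which was to limit gestational weight gain.

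**What to change.** Rewrite the paragraph under Statistical analyses so that it states:

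- **Study A, primary:** child BMI SDS compared between the LiP intervention and control arms as randomised. Saying as randomised matters because the section on numbers describes the groups by whether mothers took part in the intervention.
- **Study B, primary:** child BMI SDS compared between the obese LiP control group and the normal-weight reference group, adjusted for pre-pregnancy confounders.
- **Other variables:** in Study A, pregestational BMI may serve as a baseline covariate or effect modifier. Analyses by gestational weight gain are labelled secondary or exploratory, and weight gain is not adjusted for as a confounder in either primary analysis.

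Further model detail, such as whether hospital is a covariate, can be left to the statistical analysis plan.

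The cost is one reworded paragraph in a protocol amendment. Arm and group membership are already part of the design, so no further data are needed. The sample size and the 0.42 SDS statement stay as they are, and then describe the analyses actually named.
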